#### Intervention group

The intervention group received KYCT weighing 0.3g per tablet, manufactured by Beijing Qinuo Biotechnology Company Limited. Participants took 1.2g per dose (4 Tablet) twice daily, with warm water 30 minutes after meals.

During the trial, all participants received standard care, including (1) dietary control, including adopting a low-calorie diet, maintaining ideal body weight, avoiding high-purine foods, strictly abstaining from all kinds of alcohol, and drinking at least 2000 ml of water per day; (2) trigger avoidance, including quitting smoking, avoiding overeating, avoiding excessive fatigue and mental stress, and avoiding the use of drugs that severely affect uric acid excretion, such as some diuretics; (3) prevention and treatment of comorbidities, including hyperlipidemia, diabetes, hypertension, coronary heart disease, cerebrovascular disease, etc.

During the trial, all participants were provided with a uniform treatment medication for gout attacks: 60 mg of Etoricoxib Tablet (manufactured by Hangzhou MSD Pharmaceutical Co., Ltd., China, 60 mg/tablet, Batch No. J20180059), taken once daily, with a 7-day supply provided to patients at the time of enrollment.

The study medication was immediately discontinued if SUA levels were <180 umol/L during the visit.

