### Result assessment

Evaluators assessed all relevant indicators at baseline, 4th, 8th, and 12th week. Details of the assessments are provided in **Table 1**.

**Table 1 T1:** Schedule for data collection, the process of the assessments per visit.

measures	Baseline	Intervention phase		
Time(weeks)	-2-0	4	8	12
Informed consent	**✓**			
Demographics and Past medical history	**✓**			
Physical examination	**✓**	**✓**	**✓**	**✓**
Laboratory Tests	**✓**	**✓**	**✓**	**✓**
Electrocardiogram	**✓**			**✓**
Acertainment of Inclusion and Exclusion Table	✓			
Distribution of the study medicine		✓	✓	
Drug recovery		✓	✓	✓
Routine follow-up measurement table		✓	✓	✓
Adverse events		✓	✓	✓
Endpoint events		✓	✓	✓
Medication adherence assessment		✓	✓	✓

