#### Efficacy endpoints

##### Primary efficacy endpoint

The proportion of participants who maintained SUA levels <420 umol/L at week 12 (SUA levels were uniformly determined by uricase-peroxidase coupling assay, as described in Appendix 1).

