### Data analysis

The complete analysis set (FAS) and per protocol set (PPS) were used for efficacy evaluation analysis. The safety set (SS) was used for safety indicator analysis; since concomitant medications may affect efficacy and safety, the overall combination therapy was analyzed using the SS. General data was analyzed using the FAS and PPS. The last observation was carried forward for efficacy analysis for participants who withdrew prematurely. Dropouts with baseline data were included in efficacy analyses using the last observation carried forward. Excluded cases were not included in the efficacy statistical analysis, but those who received at least one treatment and had at least one safety record participated in the adverse reaction analysis.

To address potential confounding from lifestyle modifications, we will implement a three-pronged strategy to differentiate the specific effects of KYCT from those attributable to dietary control and health education. First, the double-blind placebo-controlled design ensures both groups receive identical lifestyle interventions, with KYCT administration being the sole therapeutic distinction between arms. Second, our primary analysis will employ analysis of covariance (ANCOVA) adjusting for key lifestyle covariates including physical activity levels (measured in MET-minutes/week) and daily purine intake (quantified through 24-hour dietary recalls). Third, sensitivity analyses will examine treatment effects in predefined adherent subgroups (≥80% protocol compliance for both medication intake and lifestyle recommendations) to assess outcome robustness against potential lifestyle adherence variations.

Furthermore, to address potential heterogeneity in treatment effects across subpopulations, three methodological safeguards have been incorporated: First, stratified randomization by baseline sUA tertiles (7.0-7.5, 7.6-8.5, >8.5 mg/dL) and sex ensures balanced subgroup distributions. Second, pre-specified Bayesian hierarchical models with regularizing priors [N(0,1)] will estimate subgroup effects while pooling information across multicenter clusters. Third, all subgroup comparisons will apply Benjamini-Hochberg FDR correction (<10%) within stratification categories, with results explicitly interpreted as exploratory hypotheses per CONSORT extension guidelines.

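### The primary analysis adjusts for activity and purine intake without fixing when they are measured; if on-trial values are used, the estimate can move away from the randomised effect

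*Protocol article*

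**What the plan says.** In the protocol article, Data analysis, the authors open the relevant paragraph with "To address potential confounding from lifestyle modifications, we will implement a three-pronged strategy". There are three parts.

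- The first is the design itself: "the double-blind placebo-controlled design ensures both groups receive identical lifestyle interventions, with KYCT administration being the sole therapeutic distinction between arms".
- The second is the model: "our primary analysis will employ analysis of covariance (ANCOVA) adjusting for key lifestyle covariates", namely "physical activity levels (measured in MET-minutes/week) and daily purine intake (quantified through 24-hour dietary recalls"). No visit or time window is attached to either measure.
- The third is a sensitivity analysis in participants who complied with at least 80% of both medication and lifestyle recommendations.

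Under Intervention measures, lifestyle care is part of the treatment period for everyone, for example "dietary control, including adopting a low-calorie diet, maintaining ideal body weight, avoiding high-purine foods". The primary endpoint is binary: "The proportion of participants who maintained SUA levels <420 umol/L at week 12". Table 1 has no row that names a dietary recall or an activity measure. One generic row, "Routine follow-up measurement table", is ticked at weeks 4, 8 and 12.

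**The concern.** A covariate in the primary model of a randomised trial should be one that treatment cannot have affected. Activity and purine intake meet that condition only if they are measured before randomisation. The text leaves the time open, and its rationale favours the wrong choice, because baseline values cannot capture changes in lifestyle made during the trial.

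If on-trial values are used, two things can happen. Any part of the treatment effect that runs through diet or activity is taken out of the estimate. In addition, because on-trial lifestyle and SUA share causes such as motivation, conditioning on lifestyle can make the arms differ on those causes even though randomisation balanced them. The result that decides the trial would then not be the randomised comparison of KYCT with placebo. With the time left open, the analyst could also choose it after seeing data.

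**Working it through.** **Step 1: what the text implies about timing.** The adjustment is meant to separate KYCT from dietary control and health education. Both are delivered during the intervention. The third part of the same strategy selects on compliance with lifestyle recommendations, which can be observed only on trial. On-trial values are therefore the natural reading, but this is an inference.

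**Step 2: whether the confounding exists.** Confounding of a randomised comparison by a co-intervention needs the co-intervention to differ by arm for reasons other than treatment. The first part of the strategy says that it does not differ. The second part therefore adjusts for a problem that the first has already dealt with.

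**Step 3: whether treatment could move lifestyle.** SUA is measured at weeks 4, 8 and 12, and study medication is stopped when a visit value is below 180 umol/L, so sites see results during the trial. Those results could influence counselling or behaviour. Blinding weakens this route but does not close it. The article does not say that participants are told their results.

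**Step 4: direction and size, by illustration.** No input below comes from the documents; all are assumed. T is treatment (0/1), L0 baseline lifestyle, U an unmeasured common cause, L1 on-trial lifestyle and Y the SUA outcome on a continuous scale. L0, U and the errors e are independent standard normal.

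- L1 = 0.6·L0 + a·T + 0.5·U + 0.6·e
- Y = −0.5·T + 0.3·L1 + 0.4·U + 0.7·e

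Within an arm, var(L1) = 0.36 + 0.25 + 0.36 = 0.97, and var(Y) = 0.09×0.97 + 0.16 + 2×0.3×0.4×0.5 + 0.49 = 0.857. The SDs are 0.98 and 0.93, so units are close to SD units.

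- Total (randomised) effect: −0.5 + 0.3a.
- Effect adjusted for L1: −0.5 − 0.4×(0.5/0.97)×a = −0.5 − 0.206a.
- Difference: −0.506a, of which −0.3a is the removed pathway and −0.206a is common-cause bias.

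A simulation with 63 per arm and 4,000 runs agrees:

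| Shift a | Total effect | Adjusted for L0 (simulated) | Adjusted for L1 (formula / simulated) | L1-adjusted (formula) minus total |
|---|---|---|---|---|
| 0 | −0.50 | −0.498 | −0.500 / −0.499 | 0 |
| −0.2 | −0.56 | −0.564 | −0.459 / −0.460 | +0.10 |
| −0.4 | −0.62 | −0.617 | −0.418 / −0.416 | +0.20 |
| +0.2 | −0.44 | −0.440 | −0.541 / −0.539 | −0.10 |
| +0.4 | −0.38 | −0.377 | −0.582 / −0.580 | −0.20 |

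Baseline adjustment recovers the total effect throughout. On-trial adjustment does so only at a = 0. The sign of the error follows the sign of the shift, so the drug can look worse or better than it is.

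**The case against.** **The timing is not stated.** This stands. A reader might infer that the plan definitely conditions on on-trial values, but the text does not say that. Inclusion requires at least a month of low-purine diet before enrolment, so a baseline purine measure is plausible. If baseline was meant, the model is sound in this respect and needs only to say so.

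**Table 1 proves little.** This also stands. A reader might infer from the missing rows, or from a follow-up form that is not ticked at baseline, that no baseline values exist. Table 1 uses generic rows throughout; SUA, lipids and waist circumference have no named row either, and patient logs are mentioned elsewhere. The table does not show when diet or activity was recorded.

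**The size is unknown.** A reader might attach a percentage. For example, assume a direct effect of −60 umol/L, a 0.3 SD shift in purine intake, 15 umol/L per SD, and a common cause with coefficients 0.5 on intake and 25 on SUA. The total effect is −60 + 15×0.3 = −55.5 and the adjusted effect −60 − 25×0.5×0.3 = −63.75, about 15% larger. That figure rests wholly on the assumed shift, in a blinded trial with identical lifestyle care. It is also on a continuous scale, while the endpoint is a proportion. The documents support no such number.

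**Perhaps the direct effect is wanted.** The authors do speak of isolating the specific effect of KYCT. Adjusting for on-trial lifestyle does not deliver that either when there is a common cause: at a = −0.4 the direct effect is −0.50 and the adjusted estimate −0.418.

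**Missing recalls.** A reader might expect participants without recalls to drop out of the primary analysis. The article states neither a missing rate nor how missing covariates are handled, so this cannot be held against it.

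**Conclusion.** The point holds in a limited form. The primary analysis names two lifestyle covariates, leaves their measurement time open, and justifies them by a form of confounding that the randomised design already prevents. If on-trial values are used and the arms come to differ in diet or activity, the estimate can depart from the randomised effect in either direction.

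The amount cannot be determined from the documents. In the linear illustration it is nil without a between-arm shift and about half the shift otherwise. That ratio depends on assumed coefficients and does not carry over directly to the difference in responder proportions. The problem is worth correcting because it sits in the primary analysis and costs little to remove. Nothing here shows that the trial's result will be biased.

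**What to change.** Make the following changes in Data analysis, before the first unblinding.

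1. Restrict the primary model to covariates measured before randomisation: baseline SUA and the stratification factor sex. Use a model suited to a binary week-12 outcome, such as logistic regression. The article already adjusts its MCID responder analysis by logistic regression for baseline SUA and the stratification factors, so this also makes the two analyses consistent.
2. Report on-trial physical activity and purine intake descriptively by arm at the visits where they were recorded. That shows directly whether lifestyle diverged.
3. Keep lifestyle covariates for a supplementary analysis, with baseline values if these were collected. The article says recruitment ended in July 2023, so baseline values that were not recorded cannot be recovered. In that case, omit the baseline-adjusted version.
4. If baseline values were intended all along, say so. They may still be better placed in the supplementary analysis.

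The cost is a change of wording. No new data and no change in sample size are needed, and the primary result no longer depends on dietary recalls.

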### Inclusion criteria

(1) Age 18–70 years (at the time of obtaining informed consent), any gender; (2) Meet the diagnostic criteria for asymptomatic HUA; (3) Blood uric acid level > 8.0 mg/dL (480 μmol/L) at enrollment after 1 month or longer of low purine dietary control; (4) No history of acute gout attack before enrollment; (5) Normal electrocardiogram at enrollment; (6) Able to swallow Tablet; (7) Voluntarily participate, able to comply with regular follow-up and complete patient logs, and sign an informed consent form.

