### Sample size calculation

According to the literature of Dalbeth N (25), Zhang X (26) et al., assuming that the effective rate of the experimental group is about 60% and the effective rate of the control group is about 30%, the sample size with a power of 0.8 was calculated to detect the difference between the two groups in terms of the effective rate, using the formula for comparing two sample proportions (27). The power of the test (1-β) was set at 0.8, and the significance level (Type I error rate) was set at 0.05 for a two-sided test. The sample size was estimated to be 53 per group, considering a dropout rate of 15%, resulting in a total of 126 participants, with 63 participants per group.

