##### Secondary efficacy endpoints

Proportions of participants maintaining sUA level <360 umol/L at week 12; percent change of sUA level from baseline to each visit; maximal percent change of sUA level from baseline to week 12; changes in anthropometric parameters (body weight, waist circumference, hip circumference, BMI), blood pressure, lipid profile, and fasting blood glucose level; number of gout flares reported; proportion of participants with gout flares cumulatively assessed at each visit.

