Statistical analysis was performed using SPSS 20.0 software. We presented the results as mean ± standard deviation for quantitative data that followed a normal distribution. We used an independent sample t-test to compare differences between the two groups and a paired sample t-test to compare differences within each group before and after the intervention. We presented the results as the median and interquartile range for quantitative data that followed a skewed distribution. We used the Mann-Whitney test to compare differences between the two groups and the Wilcoxon test to compare differences within each group before and after the intervention. We used Spearman correlation analysis to examine the correlation between variables. A significance level of P < 0.05 was considered statistically significant.

The proportion of participants attaining the MCID (≥1.2 mg/dL sUA reduction) will be compared between treatment arms using logistic regression, adjusted for baseline sUA levels and stratification factors (sex, baseline sUA tertiles). Results will be interpreted as hypothesis-generating, with 95% confidence intervals reported to quantify precision. Sensitivity analyses will assess MCID consistency across predefined subgroups (baseline sUA strata, renal function categories).

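### Continuous endpoints: within-arm before-after tests are inferential and cannot test KYCT against placebo, and the between-arm tests are chosen by observed distribution without adjustment for baseline or stratification factors

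*Protocol article*

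**What the plan says.** All references are to the protocol article.

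- **Within arms (Data analysis).** For normally distributed data the plan is "a paired sample t-test to compare differences within each group before and after the intervention". The Wilcoxon test replaces it for skewed data.
- **Between arms (Data analysis).** "We used an independent sample t-test to compare differences between the two groups" covers normal data. For skewed data: "We used the Mann-Whitney test to compare differences between the two groups and the Wilcoxon test to compare differences within each group". No covariate is named for either.
- **Choice of test (Data analysis).** It follows the observed distribution, as does the summary statistic: "median and interquartile range for quantitative data that followed a skewed distribution". One threshold, P < 0.05, covers all these tests. The MCID analysis in the same section is labelled hypothesis-generating; the within-arm tests carry no such label.
- **Endpoints (Secondary efficacy endpoints).** They include "percent change of sUA level from baseline to each visit", the maximal percent change to week 12, and changes in body measures, blood pressure, lipids and fasting glucose.
- **Population and care.** Entry requires "Blood uric acid level > 8.0 mg/dL (480 μmol/L) at enrollment", measured after at least a month of low-purine diet (Inclusion criteria). Both arms then receive diet and lifestyle control (Intervention measures).
- **Planning assumption (Sample size calculation).** "the effective rate of the control group is about 30" per cent, with 53 per arm before dropout.
- **Adjustment elsewhere (Data analysis).** An ANCOVA is tied to the primary analysis and names physical activity and purine intake as covariates. Baseline SUA is a named covariate only in the exploratory MCID logistic model. Randomization is stratified by sex and baseline SUA.

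**The concern.** The study objective is that KYCT outperforms placebo. A before-after test inside one arm has no comparator. It mixes any drug effect with regression to the mean, which follows from selecting on a high SUA, and with the lifestyle measures given to everyone. The article's own limitations paragraph concedes that lifestyle change may confound effects attributed to KYCT. With the tests at P < 0.05 and not marked descriptive, a report could state that KYCT significantly lowered SUA from baseline when an inert tablet would probably have given the same statement.

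The between-arm tests are the right kind of comparison, but two features weaken them. They adjust neither for the baseline value nor for the stratification factors. And the choice between a t-test (means) and a Mann-Whitney test (ranks) waits for the data, so what is estimated for each endpoint is not fixed beforehand.

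**Working it through.** The document gives no SD, correlation or target difference for any continuous endpoint, so there is no figure of the plan to reproduce here. The 53 per arm belongs to the binary primary endpoint and serves below only as the arm size (its dropout step reproduces: 53/0.85 = 62.4, so 63 per arm).

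**1. Chance of a significant within-arm SUA fall on placebo**

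From the document: n = 53, two-sided 0.05, entry above 480, control rate 30%, read as SUA < 420 at week 12.

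Assumed: week-12 SUA roughly normal with SD 60 to 100; baseline mean 500 to 540; baseline SD 30, 40 or 100; baseline/week-12 correlation r = 0.3 or 0.5.

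- Week-12 placebo mean = 420 + 0.524 × SD = 451.5, 462.0 and 472.4 for SD 60, 80 and 100.
- Fall = baseline mean − week-12 mean.
- SD of change = √(SD0² + SD12² − 2·r·SD0·SD12).
- Noncentrality = fall / SD of change × √53; power from the noncentral t with 52 df.

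Worked case (baseline mean 520, SD12 = 100, SD0 = 30, r = 0.3): fall = 47.6; SD of change = √(900 + 10000 − 1800) = 95.4; noncentrality = 47.6/95.4 × 7.28 = 3.63; power 0.945.

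Fall in umol/L, then the range of power over the assumed baseline SDs and correlations:

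| Baseline mean | SD12 = 60 | SD12 = 80 | SD12 = 100 |
|---|---|---|---|
| 500 | 48.5; 0.93–1.00 | 38.0; 0.71–0.98 | 27.6; 0.38–0.62 |
| 510 | 58.5; 0.99–1.00 | 48.0; 0.89–1.00 | 37.6; 0.62–0.87 |
| 520 | 68.5; 1.00 | 58.0; 0.97–1.00 | 47.6; 0.82–0.97 |
| 540 | 88.5; 1.00 | 78.0; 1.00 | 67.6; 0.98–1.00 |

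The low ends come from baseline SD 100, which is hard to square with a mean only 20 to 40 above a floor of 480. With baseline SD 30 or 40, the cell for mean 510 and SD12 = 100 is 0.80–0.87.

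**2. Regression to the mean alone**

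Simulating selection above 480 from an assumed population (mean 400 to 480, SD 80, correlation 0.70 to 0.85), with no real change in anyone, gives a mean fall of 9.7 to 36.6 umol/L and power 0.37 to 0.995. Only 1.7 to 14.7% then end below 420, so under these assumptions a 30% control rate implies a further fall on placebo.

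**3. Metabolic endpoints**

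Participants are not selected on these variables and no control-arm change is assumed for them. The calculation cannot be done.

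**4. What baseline adjustment would gain**

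On the absolute-change scale, with equal baseline and follow-up SDs, the residual variance factors are 2(1 − r) for a change score and 1 − r² for ANCOVA. Their ratio is (1 + r)/2, a reduction of (1 − r)/2:

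- r = 0.3: 35%
- r = 0.6: 20%
- r = 0.9: 5%

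For SUA the entry threshold narrows the baseline. With assumed SDs of 40 (baseline) and 80 (week 12):

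- r = 0.3: 5824/6080 = 0.96, a gain of 4%
- r = 0.5: 4800/4800 = 1.00, no gain

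**The case against.** Several stronger readings are tempting, and the document does not support them.

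- **Placebo tests will be significant.** A reader might infer certainty. The table shows likely, not certain, and for SUA only. The 30% is called an effective rate with no threshold attached; linking it to < 420 is an inference from the primary endpoint. The Discussion gives that endpoint as < 6 mg/dL, about 360 umol/L on the protocol's own scale (8.0 mg/dL = 480). That reading would imply a larger placebo fall, so it does not weaken the point. The qualifying SUA follows at least a month of diet, so part of the diet effect may already be in the baseline.
- **The between-arm tests ignore baseline.** They do not. The endpoints are changes or percent changes, so baseline enters by subtraction or division. What is absent is adjustment.
- **Test choice could be steered towards KYCT.** The two-step unblinding keeps the arms as A and B until the analysis is complete, which limits this. The objection that remains is that the estimand is not fixed.
- **Efficacy will be judged on within-arm P-values.** No section says so. The stated hypotheses are comparative, and the primary endpoint is a proportion that these tests do not touch.

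It can also be said that stratifying by baseline SUA and sex limits imbalance in SUA, and that an ANCOVA is planned. The first is fair for SUA but does not cover lipids, glucose or blood pressure. The second does not settle the matter: the ANCOVA is tied to a primary analysis whose endpoint is binary, names only lifestyle covariates, and is not reconciled with the unadjusted tests. Nor is this detail left to an analysis plan, since the article states the methods.

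**Conclusion.** The point holds as a free improvement to the secondary analyses. The plan gives within-arm tests the standing of inference, although under its own 30% control rate (read as < 420) a significant placebo SUA fall is likely: roughly 0.8 to 1.0 under most assumed SDs with baseline mean 510 or more, and about 0.4 to 0.6 with baseline mean 500 and week-12 SD 100. Those figures rest on assumed means, SDs and correlations. Nothing comparable can be claimed for the metabolic endpoints.

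The between-arm tests are valid comparisons but leave precision unused: 20 to 35% of variance at r = 0.6 to 0.3, about 5% at r = 0.9, and about 0 to 4% for SUA. For SUA the benefit is therefore mainly a fixed estimand and protection from residual chance imbalance. The primary endpoint is unaffected.

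**What to change.** 1. Report within-arm changes descriptively (mean or median change with its spread) and delete the paired t and Wilcoxon tests as inferential tests.
2. For each continuous endpoint, name one between-arm model in advance: a linear model of the change (percent change for SUA, at each visit, and likewise for the maximal percent change) on arm, the baseline value of that endpoint, sex and baseline SUA stratum. For SUA endpoints, enter baseline SUA once, as a continuous covariate. Report the adjusted difference with a 95% confidence interval.
3. Use a log or rank analysis only for endpoints named beforehand, not on inspection of the distribution.
4. Reconcile the ANCOVA paragraph with the t-test and Mann-Whitney paragraph: say which endpoints each governs and whether baseline is a covariate. Define the SUA stratum as actually used, since the lowest stated band (7.0–7.5 mg/dL) lies below the entry threshold of 8.0 mg/dL.

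The cost is analysis wording only. The baseline values, sex and strata are already collected.
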